### Data collection

At baseline session, the CRN will collect clinical data from the medical records of all consented patients that will include current cancer stage, time since diagnosis, treatment intent, testosterone level, prostate specific antigen level, Gleason score, comorbidity index. The SRA will collect sociodemographic data including age, marital status, ethnicity, living arrangement, education, work status, alcohol consumption and smoking history.

At baseline and 6-month follow-up visits, the primary outcome variable of *cognitive function* including memory, attention and working memory, and executive function will be assessed by the CPRA using well-established neurocognitive tests. Additionally, each participant will complete a standardized “effort test” to ensure validity of the test results. A minimum of 6 months between tests is required to prevent practice or carry-over effects. *Memory* will be assessed using: (1) the Brief Visuospatial Memory Test - Revised (BVMT-R) [44] for non-verbal memory, and (2) the California Verbal Learning Test, 2^nd^ Edition (CVLT-II) [45] for verbal memory. *Attention and working memory* will be assessed using: (3) the Digit Span and Letter-Number Sequencing tasks from the Wechsler Adult Intelligence Scale – 3^rd^ Edition (WAIS-III). [46]*Executive function* will be assessed using: (4) the Stroop Color and Word Test [47] for processing speed and inhibition, and (5) the Trail Making Test Parts A and B [48] for visuomotor tracking and mental flexibility. *Test-taking effort* of the neurocognitive tests will be confirmed using the (6) Word Memory Test (WMT) [49].

At baseline and all follow-up sessions (3 and 6 months), the primary (psychosocial functions) and secondary outcome variables (HRQOL) will be assessed. Cognitive function of *self-reported memory function* will be assessed using the Prospective Retrospective Memory Questionnaire (PRMQ) [50,51] for short and long-term memory. *Psychosocial function* will be assessed using: (8) the Center for Epidemiological Studies Depression (CES-D) for *depression, *[52] (9) the Spielberger State-Trait Anxiety Inventory (STAI) [53] for *anxiety*, (10) the Rosenberg Self-Esteem Scale (SES) for *self-esteem*. [54,55]*HRQOL* will be assessed using (12) the Functional Assessment of Cancer Therapy Prostate Module (FACT-P) [56] as a disease-specific global HRQOL instrument. Every four weeks, physical activity levels of both Control and Exercise groups will be monitored based on the completed pedometer daily logs returned by all participants.

#### Exercise group

*Exercise adherence* of the Exercise Group participants will be monitored using the exercise daily logs returned every four weeks, and phone surveys conducted by SRA every two weeks. The phone surveys will also be used to monitor *exercise safety and progress*.

## Statistical analysis

### Primary outcome variables

A mixed between-within-subjects multivariate analysis of variance (MANOVA) (Group X Time) will be conducted to determine if there is a significant interaction between the between-subjects (Group) and within-subjects (Time) comparisons for:

cognitive function based on the neurocognitive tests at baseline and 6-month follow-up session;

psychosocial function at baseline, 3- and 6-month follow-up sessions;

### Secondary outcome variables

Pearson product–moment correlation will be conducted to determine the association between HRQOL and primary outcome variables (cognitive and psychosocial functions).

For The Exercise Group, Spearman-Rank Or Pearson Product–Moment Correlations Will Be Performed To Determine If Baseline Sociodemographic, Clinical, Psychosocial, And Physical Activity Factors Are Significantly Associated With Exercise Adherence (Average Percentage Of Adherence To The Target Exercise Frequency, Duration And Intensity Based On The Exercise And Pedometer Daily Logs).

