**Discussion:**

The significance of the cognitive-psychosocial side effects of ADT in men with prostate cancer has only been recently recognized, and the management remains unclear. This study addresses this issue by designing a simple and accessible home-based, exercise program that may potentially have significant impact on reducing the cognitive and psychosocial side effects of ADT, and ultimately improving the health-related quality of life in men with prostate cancer receiving ADT.

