#### Baseline assessment session

The SRA, who is trained in health sciences field, will contact the participants to schedule a baseline assessment in coordination with a clinical psychology research assistant (CPRA), who is trained to administer neuropsychological tests.

The baseline assessment will be administered by the CPRA first, followed by the SRA. The CPRA will collect the sociodemographic characteristics, and administer the primary (cognitive-psychosocial functions) and secondary outcome measures (health related quality of life (HRQOL)). The SRA will collect data on the physical activity variables.

The CPRA will be blinded to the group assignments of the participants. After the baseline assessment, the SRA will assign the participant the first available number from a randomly generated list consisting of “1” and “2”, that are generated by mixed randomization, [38] using both simple randomization and permuted-block methods. Number “1” is designated as the Exercise Group that will receive instructions in setting up an individualized 6-month home-based walking exercise program in addition to their daily activities. Number “2” is designated as the Control Group that will be advised to perform daily activities as usual and follow the standard medical advice from their attending physician.

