#### Follow-up sessions

The CPRA will schedule follow-up sessions for all participants at 3 and 6 months after ADT initiation. At 3 months, primary outcome (psychosocial functions) and secondary outcome variables (HRQOL) will be re-assessed. At 6 months, all primary (cognitive and psychosocial functions) and secondary (HRQOL) outcome measures will be re-assessed.

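### HRQOL is the named secondary outcome in both arms, but the plan only correlates it with the primary outcomes and states no between-group comparison

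*Protocol article*

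**What the plan says.** All references are to the protocol article.

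- **Status of HRQOL.** Under *Baseline assessment session*, the blinded assessor is to "administer the primary (cognitive-psychosocial functions) and secondary outcome measures (health related quality of life (HRQOL". *Data collection* names the instrument as "the Functional Assessment of Cancer Therapy Prostate Module (FACT-P".
- **When it is measured.** *Data collection* states: "At baseline and all follow-up sessions (3 and 6 months), the primary (psychosocial functions) and secondary outcome variables (HRQOL) will be assessed". *Follow-up sessions* adds that at 6 months "all primary (cognitive and psychosocial functions) and secondary (HRQOL) outcome measures will be re-assessed".
- **In whom.** *Follow-up sessions* states: "The CPRA will schedule follow-up sessions for all participants at 3 and 6 months after ADT initiation". Both arms therefore contribute FACT-P at all three visits.
- **Between-group model.** Under *Primary outcome variables*: "A mixed between-within-subjects multivariate analysis of variance (MANOVA) (Group X Time) will be conducted". Two targets follow: cognitive function (baseline and 6 months) and psychosocial function (baseline, 3 and 6 months).
- **HRQOL analysis.** Under *Secondary outcome variables*, a Pearson correlation "will be conducted to determine the association between HRQOL and primary outcome variables (cognitive and psychosocial functions". The other item there concerns correlates of adherence within the Exercise Group.
- **Place of HRQOL in the rationale.** The abstract's *Discussion* says that the programme may reduce side effects of ADT, "ultimately improving the health-related quality of life in men with prostate cancer receiving ADT". The objective at the end of *Background* names cognitive-psychosocial functions only.

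**The concern.** The trial randomises men in order to compare exercise with control. An outcome called secondary and collected on the same schedule in both arms would normally be compared between those arms. Here the statistical section gives it an analysis with no group term. That analysis asks whether men with better mood or cognition also report better HRQOL. This could be asked of any cohort, and the answer says nothing about what exercise does.

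At stake is the only randomised evidence the trial could offer on HRQOL. A team following the published plan would report correlations and no treatment difference. A reader could then take a correlation between FACT-P and a primary outcome as support for the benefit the abstract hopes for. If a between-group result were reported later, it would not be traceable to the published plan.

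**Working it through.** The article gives a total of 20 men and no power, effect size or SD, so there is no stated figure to reproduce. The main check is a reading; the arithmetic shows size only.

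**1. Which analysis is assigned to which outcome**

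| Outcome | Status | Visits | Arms | Stated analysis | Group term? |
|---|---|---|---|---|---|
| Neurocognitive tests | Primary | Baseline, 6 months | Both | Group by Time MANOVA | Yes |
| Psychosocial scales | Primary | Baseline, 3, 6 months | Both | Group by Time MANOVA | Yes |
| HRQOL (FACT-P) | Secondary | Baseline, 3, 6 months | Both | Pearson correlation with primary outcomes | No |

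No other section of the article compares HRQOL between arms.

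**2. Can the correlation stand in for a comparison?**

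Assumptions, not in the article: 10 men per arm, one value per man, within-arm SD 1 for both measures, arms pooled. Let exercise shift HRQOL by *d* SD and leave the primary outcome unchanged, with within-arm correlation ρ. With equal arms the shift adds d²/4 to the variance of HRQOL and nothing to the covariance, so

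pooled r ≈ ρ / √(1 + d²/4).

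| ρ | d | Formula | Simulated mean (20,000 runs) |
|---|---|---|---|
| 0 | 0 | 0 | 0.00 |
| 0 | 1 | 0 | 0.00 |
| 0.5 | 0 | 0.50 | 0.49 |
| 0.5 | 1 | 0.5/√1.25 = 0.45 | 0.43 |

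A full 1 SD effect on HRQOL leaves the correlation almost unchanged.

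In the opposite case both measures shift by 1 SD and are unrelated within arm. The covariance is then 1/4 and each variance 1 + 1/4, so r = 0.25/1.25 = 0.20. An association appears that comes only from the arms, although it is below the two-sided 5% critical value of about 0.44 for 20 men. This is the reason to adjust any retained correlation for group.

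**3. What a between-group comparison could deliver**

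Same assumption of 10 per arm, two-sided 5%, no dropout, before any gain from baseline adjustment.

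- Standard error of the difference: √(2/10) = 0.447 SD.
- Half-width of the 95% CI: 1.96 × 0.447 = 0.88 SD.
- Detectable with 80% power: (1.960 + 0.842) × 0.447 = 1.25 SD by the normal approximation; 1.32 SD by the t distribution.
- Power (normal approximation): 20% at 0.5 SD, 43% at 0.8 SD, 61% at 1.0 SD.

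**The case against.** **HRQOL is outside the stated objective.** The objective covers cognitive and psychosocial functions, and the closing *Discussion* restates the aim that way. Relating HRQOL to those functions is a coherent, if limited, secondary question. This stands as a limit on weight: nothing here touches the primary conclusion. It does not remove the point, because the article itself calls HRQOL a secondary outcome in several sections and measures it in both arms.

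**An article may leave detail to an analysis plan.** This would answer a silence. Here the article has a section for secondary outcomes and fixes an analysis there, while the between-group model lists its targets and omits HRQOL. An unseen plan that compared FACT-P between arms would be adding to the published text.

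**The gain is modest.** With 20 men the interval will be wide. That is true, and it argues for an estimate with its CI rather than a test, not for leaving the comparison out.

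**Stronger readings that the article does not support.**

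- A reader might infer that the trial cannot say whether exercise changes HRQOL. The data would support a comparison; only the written analysis lacks one.
- A reader might infer that improved HRQOL is a planned claim. The abstract's sentence is hedged and describes a hoped-for downstream benefit.
- A reader might infer that the correlation treats repeated visits on one man as independent. The article does not say which visits enter, whether change scores are used, or whether arms are pooled. That is detail an article may leave out, so no error can be charged on it.

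**Conclusion.** The point holds as a gap between the outcome and its stated analysis. HRQOL is a named secondary outcome, measured at three visits in both arms, and the plan as written yields no between-group estimate for it. The correlation is no substitute: under the assumptions shown, a 1 SD effect of exercise on HRQOL moves it from about 0.00 to 0.00, or from 0.49 to 0.43.

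The textual part needs no assumption. The sizes assume 10 per arm and SD 1, which the article does not give; its mixed randomisation scheme may not produce exactly equal arms. The consequence is confined to the secondary outcome. It should be corrected, but it does not threaten the primary analysis.

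**What to change.** Under *Secondary outcome variables*:

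1. Add a between-group comparison of FACT-P total at 6 months, with 3 months as supportive. Either adjust for baseline FACT-P, or place FACT-P in the existing Group by Time framework and report the between-group difference in change. Give the difference with its 95% CI and say in advance that it will be imprecise with 20 men.
2. Keep the correlation of HRQOL with the primary outcomes, labelled exploratory, using one value per man (for example change from baseline to 6 months) and adjusting for group.

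The cost is one more model and a few lines of analysis wording. No new data, visits or participants are needed.

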**Methods:**

A 6-month prospective, single-blinded, randomized controlled trial will be conducted to compare the Exercise Group with the Control Group. Twenty men with prostate cancer starting ADT will be recruited and randomly assigned to one of the two groups: the Exercise Group will receive instructions in setting up an individualized 6-month home-based, walking exercise program, while the Control Group will receive standard medical advice from the attending physician. The primary outcomes will be psychosocial and cognitive functions. Cognitive functions including memory, attention, working memory, and executive function will be assessed using a battery of neurocognitive tests at baseline and 6 months. Psychosocial functions including depression, anxiety and self-esteem will be assessed at baseline, 3 and 6 months using the Center for Epidemiological Studies Depression Scale, Spielberger State-Trait Anxiety Inventory, and Rosenberg Self-Esteem Scale*.*

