#### Recruitment

A total of 20 patients will be recruited consecutively during office visits at the initial 3-month phase of the study at CancerCare Manitoba. The attending physician will screen the patients for inclusion criteria (men aged 50 or older, diagnosed with adenocarcinoma prostate cancer, will initiate and receive continuous ADT (LHRH or combination of LHRH and anti-androgen for at least 6 months). The physicians will be provided with an information sheet that provides brief information about study. If the patients meet the preliminary inclusion criteria, the physicians will provide a brief explanation about the study, and verbal consent to refer them to a clinical research nurse. The clinical research nurse will confirm that all inclusion and exclusion criteria are met, explain the study protocol, provide an information sheet for patients, and obtain written informed consent from the patients who would like to participate in the study. The clinical research nurse will provide the student research assistant (SRA) with the signed consent forms and contact information of the consented patients of the study.

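### Deciding by significance which baseline factors relate to adherence, in about 10 exercise-arm men, would often flag a false association and overstate its size; estimate and label as exploratory instead

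*Protocol article*

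**What the plan says.** The second analysis under Secondary outcome variables is confined to the Exercise Group. There, "Spearman-Rank Or Pearson Product–Moment Correlations Will Be Performed To Determine" whether baseline factors from four domains (sociodemographic, clinical, "Psychosocial, And Physical Activity Factors Are Significantly Associated With Exercise Adherence"). Adherence is an average percentage taken over exercise frequency, duration and intensity. The article gives no significance level, no adjustment and no shortlist of factors for this analysis, and does not call it exploratory.

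The candidate factors are listed elsewhere in the article:

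- Data collection, clinical: "current cancer stage, time since diagnosis, treatment intent, testosterone level, prostate specific antigen level, Gleason score, comorbidity index".
- Data collection, sociodemographic: "age, marital status, ethnicity, living arrangement, education, work status, alcohol consumption and smoking history".
- Abstract, Methods, psychosocial: "Psychosocial functions including depression, anxiety and self-esteem".
- Baseline assessment session and Exercise group protocol: physical activity variables, including a self-reported activity level.

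On numbers, Recruitment says "A total of 20 patients will be recruited consecutively". They are allocated to two groups "using both simple randomization and permuted-block methods", with no ratio stated.

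**The concern.** The stated purpose is a yes-or-no answer by significance, applied across four whole baseline domains in half of a 20-man trial. This has two consequences. Testing many factors makes it likely that something reaches significance by chance. Having about 10 men means that only very large sample correlations can reach significance, so moderate real associations are mostly missed and those that pass are overstated. What is at stake is how far a reported correlate of adherence can be trusted. The comparison of exercise with control on cognitive and psychosocial function does not depend on it.

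**Working it through.** The plan gives no error rate or power for this analysis, so there is no figure of its own to reproduce.

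**Inputs**
- Factors: 8 sociodemographic + 7 clinical (Data collection) + 3 psychosocial (Abstract) + at least 1 physical activity = 19.
- Men: 20 in two groups, so about 10 exercisers. Equal allocation is an assumption.
- Level: two-sided 0.05, unadjusted. This is an assumption.

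**Chance of at least one false association when none exists**

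For k independent factors this is 1 − 0.95^k:
- k = 19: 1 − 0.95^19 = 0.623, with 19 × 0.05 = 0.95 false associations expected per trial.
- k = 15: 0.537.
- k = 14: 0.512.
- k = 13: 0.487.

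Baseline factors are not independent. Simulation with 19 null normal factors, n = 10 and Pearson tests (20,000 replicates per case) gives:

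| Correlation | Among all factors | Within domains only |
|---|---|---|
| 0 | 0.62 | 0.62 |
| 0.2 | 0.58 | 0.61 |
| 0.3 | 0.55 | 0.59 |
| 0.4 | 0.49 | 0.57 |
| 0.5 | 0.44 | 0.54 |
| 0.7 | 0.32 | 0.46 |

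With correlation 0.3 among all factors, 15 factors give about 0.47 and 13 give 0.43. Making six of the 19 factors binary leaves the independent figure at about 0.62. If whichever of Pearson and Spearman is significant were reported, the independent figure would rise to 0.76.

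The result depends on the level. At 0.01 per factor, 1 − 0.99^19 = 0.174.

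The small group does not itself raise the false-positive rate: n = 8 gives practically the same figures. Its effect is on size and power.

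**Size and power at n = 10**
- The critical t on 8 degrees of freedom is 2.306, so the critical |r| is 2.306 / √(8 + 2.306²) = 0.632.
- By simulation from bivariate normal data, power is 0.13 for a true r of 0.3 and 0.33 for a true r of 0.5. The Fisher z approximation gives 0.13 and 0.31.
- When significant, the mean estimate is about 0.69 for a true r of 0.3 and 0.74 for a true r of 0.5.

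**Would adjustment rescue the decision?**
- The first Holm step is 0.05/19 = 0.0026. The critical t is 4.296, so |r| must exceed 4.296 / √(8 + 4.296²) = 0.835.
- Power at that step is about 0.05 for a true r of 0.5 and 0.01 for a true r of 0.3. The mean significant estimate for a true 0.5 rises to about 0.87.

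**The case against.** The strongest reply is that the article does not fix the rule being criticised. It states no 0.05, does not say that a single significant result suffices, and does not say that every item collected will be tested. A level, an adjustment or a shorter list may stand in a full protocol or analysis plan that is not shown, and their absence from an article is no fault. This stands, and it is why the figures above are conditional. What remains is what the article does state: the question is settled by significance, over four domains, in about 10 men. An adjustment elsewhere would control the error rate but leave almost no power, so it would not make the decision useful.

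The count can also be disputed. Marital status, ethnicity, living arrangement and work status are nominal and have no direct correlation unless recoded; without them 15 factors remain. Further items may be constant in 10 men, and at 13 the chance is below one half even under independence. In the other direction, scoring state and trait anxiety separately or using several activity variables would raise it.

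Three stronger readings are tempting, and the documents do not support them:
- A reader might infer that a false correlate is named more often than not. That fails at pairwise correlation of about 0.4 or more among all factors, at about 0.65 or more within domains, or if about six factors drop out.
- A reader might take 0.62 as the probability that a named factor is false. It is the chance of naming at least one when none is real, which is a different quantity.
- A reader might infer that the planned wellness program would be aimed at the wrong men. The Discussion calls the study as a whole a foundation for such a program; it never mentions adherence correlates or selecting men by them.

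**Conclusion.** The point holds in conditional form. Used as a significance decision at a conventional unadjusted level, this analysis would flag at least one association under no true association in roughly 0.44 to 0.62 of trials with 19 factors and pairwise correlation from 0.5 down to 0. For 13 to 15 independent factors the chance is 0.49 to 0.54. It would miss a true correlation of 0.5 about two times in three, and would overstate it when found. These figures rest on equal allocation, an assumed two-sided 0.05 per test, and approximately normal data. This is a secondary, one-arm analysis; it does not touch the primary Group by Time comparison. It is worth correcting because the change costs almost nothing and alters what the analysis can honestly conclude.

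**What to change.** Under Secondary outcome variables, replace the aim of determining whether factors are significantly associated with adherence by this: *to estimate, with 95% confidence intervals, the association of each listed baseline factor with adherence; the analysis is exploratory, all factors are reported, and no factor is declared a predictor on an unadjusted p-value.*

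A family-wise adjusted p-value (Holm, or a permutation test on the largest correlation) may be shown as context. It should not be required, because at this sample size it would almost never name anything.

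The change is one of wording and table layout and needs no extra patients or data. The downside is that the trial gives up naming significant correlates of adherence, and the intervals will be wide.
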